### Sample Size

Four hundred thirty-five participants are intended to enroll and will be randomized with a ratio of 1:1:1. The estimated sample size provides 80% power (two sided α = 0.025, considering a multiple comparison) to detect difference in the primary outcome and the proportion of participants without subclinical depression between the MoodBox group with the online psychoeducation group and the observation group in a survival analysis (assuming the minimum difference is 14%) after 8 weeks. Taking into account a predicted 20% attrition for this comparison, at least 145 participants would be needed in each group. The calculation was based on a meta-analysis that reported clinical difference between the internet-based intervention group and psychoeducation group (9), and the calculating methods were in accordance with Chow et al.'s instruction (21).

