### Statistical Consideration

Data management and statistical analysis will be conducted using SAS9.4 (SAS Institute Inc., Cary, NC, USA). The sample characteristics would be compared using chi-square test for categorical variables or using Fisher's Z test when needed; ANOVA tests for normal distributed variables; and Mann–Whitney's U test for non-normal distributed variables. Analysis of efficacy will be based on an intent-to-treat principle, comprising all participants randomized regardless of the treatment group. The Kaplan–Meier survival analysis will be used to calculate the estimated time from baseline to response during 8 weeks' follow-up.

The Cox proportional hazard regression model using the Breslow method will be used to compare estimated time to response between groups, with control for covariates such as age, gender, years of education, and disease-related conditions; also we would use the exact method as sensitive analysis in case of tied survival data. Considering the long interval between visits after week 8, we will also use maximum likelihood estimation for Cox hazard regression model following Shen's work (34) to control left interval truncated data. Secondary analyses will be performed to assess changes from baseline to the endpoint of the study on scores of scales, using mixed-effects model for repeated-measures analysis (MMRM). A *p*-value <0.05 is considered as statistically significant. The Bonferroni method will be used to control multiple comparisons of type I error inflation.

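### Plain Bonferroni for the two MoodBox comparisons is valid, but Holm would keep the same family-wise error, is never less powerful and leaves the 435 unchanged

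*Protocol article*

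**What the plan says.** Statistical Consideration in the protocol article names the multiplicity method: "The Bonferroni method will be used to control multiple comparisons of type I error inflation". The sentence does not list the comparisons it covers. The sentence before it gives the overall level, a p-"value <0.05 is considered as statistically significant".

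The Sample Size section supplies the family. Its level is "two sided α = 0.025, considering a multiple comparison", and the comparison is "between the MoodBox group with the online psychoeducation group and the observation group in a survival analysis". It adds that "The estimated sample size provides 80% power", for a smallest difference of 14%, with 20% attrition and 145 participants per group, 435 in all. The natural reading is two comparisons, MoodBox against each comparator, at 0.05/2 each.

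Study Design explains the two comparators: psychoeducation addresses a digital placebo effect, and observation addresses natural remission. The article does not say whether success needs one or both comparisons to be significant, and it mentions no stepwise method.

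**The concern.** Plain Bonferroni holds each comparison to 0.025 whatever the other one shows. Suppose MoodBox clearly beats observation and the comparison with psychoeducation gives p = 0.035. Under Bonferroni the second result is not significant. Under Holm it is, at the same family-wise error of 0.05.

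The two comparators answer different alternative explanations of a benefit, so significance on both supports a fuller claim than significance on one. The stake is power for that second result. Validity is not in question.

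**Working it through.** **Inputs from the protocol article**

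- Overall level 0.05 and Bonferroni (Statistical Consideration).
- Two-sided 0.025 and 80% power, read here as power per comparison; two comparisons sharing the MoodBox arm (Sample Size).
- 1:1:1 allocation, 145 per group, 20% attrition (Sample Size).

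**Assumptions not in the article**

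- Correlation 0.5 between the two test statistics, which is what a shared arm and equal groups give. Values of 0.3 and 0.7 are also shown.
- Both true effects at the design value, except where stated.

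**1. The plan's own figures.** 0.05/2 = 0.025, so the level used for sizing is exactly the Bonferroni level. The attrition step is also right: 145 × 0.8 = 116 evaluable per group, and 116/0.8 = 145. The 116 itself cannot be uniquely reproduced because no control-group rate is given. The comparison below does not need that rate, because it starts from the stated 80% power.

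**2. Critical values and effect on the z scale.** Two-sided 0.025 gives 2.241 and two-sided 0.05 gives 1.960. Power of 80% at 0.025 means each z-statistic has mean 2.241 + 0.842 = 3.083.

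**3. Bonferroni.** A comparison is significant if |Z| > 2.241. With both means at 3.083 and correlation 0.5:

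- each comparison: 80.0%
- both: P(|Z1| > 2.241 and |Z2| > 2.241) = 68.7%
- at least one: 80.0 + 80.0 − 68.7 = 91.3%

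**4. Holm.** It adds the cases where one statistic exceeds 2.241 and the other lies between 1.960 and 2.241. The probability of this for a named comparison is P(1.960 < |Z1| ≤ 2.241 and |Z2| > 2.241) = 4.56%. So:

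- each comparison: 80.0 + 4.56 = 84.6%
- both: 68.7 + 2 × 4.56 = 77.8%
- at least one: 91.3%, unchanged, because Holm's first step is the Bonferroni test

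**5. Other cases (correlation 0.5 unless stated).**

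| Case | Bonferroni | Holm |
|---|---|---|
| Both effects at design value, both significant | 68.7% | 77.8% |
| The same, correlation 0.3 | 66.6% | 76.6% |
| The same, correlation 0.7 | 71.3% | 79.4% |
| Only one effect real, power for that one | 80.0% | 80.2% |
| Neither effect real, family-wise error | 4.65% | 4.65% |

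The gain for both is therefore about 10 points at correlation 0.3, 9 at 0.5 and 8 at 0.7. The figures in steps 3 to 5 are bivariate normal probabilities; simulation with 4 million draws at correlation 0.5 agrees to within about 0.1 point.

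**6. Sample size.** Holm's first step uses the same 0.025 as the sizing, so every stated property of the 435 is kept.

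**The case against.** The strongest reply is that nothing here is wrong. Bonferroni is valid, prespecified and already paid for by the sample size, and it gives simple simultaneous confidence intervals. All of that stands.

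Three stronger readings are tempting, and the article supports none of them.

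- *The 0.05 and the 0.025 conflict.* They do not. The first is the overall level that Bonferroni divides, and the second is the result of dividing it by two.
- *The design requires both comparisons to win, so about 69% is the trial's power.* Study Design gives a reason for having two comparators but sets no such rule. If both were required for a single claim, no split of alpha would be needed: each could be tested at 0.05, with P(|Z1| > 1.960 and |Z2| > 1.960) = 78.6% under the same assumptions. If either suffices, the relevant figure is 91.3%, which Holm does not change. Holm's benefit lies between these: two separate claims, with a better chance of supporting both.
- *Holm is more powerful in every situation, or psychoeducation is the harder comparison and gains most.* Holm is never less powerful, but its gain disappears or is negligible in the cases shown above. The article gives one minimum difference for both comparators, so unequal effects would be an outside assumption.

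It is also fair to say that the list of comparisons and the labelling of adjusted p-values may sit in a statistical analysis plan that is not shown. Their absence from the article is no finding. The choice of Bonferroni, however, is stated in the article and can be judged as it stands.

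**Conclusion.** The point holds as an efficiency improvement. If both effects are real at the design size, Holm gives about 4.6 points more power per comparison and about 8 to 10 points more for both, at the same family-wise error and the same 435 participants.

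The size rests on three things: reading the 80% as power per comparison, both effects at the design value, and a correlation between 0.3 and 0.7. That Holm is never worse than Bonferroni and controls the error under any dependence rests on none of these. That the family consists of the two MoodBox comparisons is an inference from the Sample Size section, though a sound one.

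**What to change.** Replace the Bonferroni sentence with Holm's procedure for the two primary MoodBox comparisons: compare the smaller p-value with 0.025 and, if it is significant, compare the other with 0.05. Name the two comparisons in the same sentence.

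Because the trial is not blinded, the change should be made and dated before anyone sees outcome data by arm. It costs one sentence, with no change to sample size, visits or conduct. The real downside is that simultaneous confidence intervals matching Holm are less simple than the 97.5% intervals (100% − 2.5%) that go with Bonferroni. If the sponsor values those intervals more than the extra power, keeping Bonferroni is defensible.

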## Discussion

Although recommendations have been made to manage subclinical depression (35, 36), most people with subclinical depression do not receive any treatment (14–16), even though the risk of subclinical depression turning into a full-blown depressive disorder is high. In recent years, in China, an increasing number of mental health professionals recommend people with subclinical depression to receive psychological interventions. However, because the number of qualified psychotherapists is limited, there is a significant lack of accessibility for people with subclinical depression in China (16). Internet-based interventions are suitable for resource-limited settings with constrained mental health services and have the potential to be scaled up, which in turn will be a solution for scalable subclinical intervention.

MoodBox combined different evidence-based psychological interventions that are established as being effective to reduce depressive symptoms, including CBT, IPT, and mindfulness meditation. The theoretical background of existing internet-based psychological interventions is primarily based on CBT. By combining multiple evidence-based interventions, MoodBox offers a more comprehensive intervention and provides more treatment options. Due to the diverse symptom presentation of people with subclinical depression, a comprehensive intervention has the potential to cover a broader range of symptoms, which in turn may have a positive impact on treatment adherence, satisfaction, and acceptability. Second, we measured mood events to provide a comprehensive understanding of the reduction of subclinical depression on preventing mood disorders. Previous research mainly focused on the efficacy of preventing depression, without paying attention to the outcome of other mental health problems. Subclinical depression is not only an early sign of major depression but also an early sign of other mental health problems, such as bipolar disorder. There is a necessity to understand how the reduction of subclinical depression can contribute to the prevention of other mood events. Another strength of the study is the use of WeChat to send out notifications to participants for follow-up information, and the implementation of the electronic data capture (EDC) system for data management. WeChat is a messaging and social media app that has been wieldy used in China, especially for adolescents. There are over one billion active monthly users of WeChat. Therefore, sending follow-up notification using WeChat is an efficient method to manage follow-up visit remotely. Additionally, participants can complete scales on their phone using the link sent via WeChat, which will allow the data directly to enter the EDC database and mitigate any error that may be caused by entering data manually. This new follow-up method can improve the quality of the trial by enacting higher requirements for quality control. Additional, ethical issues and protecting subjects' privacy are also important during the follow-up by WeChat platform, as all the research staff will sign a confidentiality agreement and operate in strict compliance with the program provisions and ethical requirements.

There are some limitations of the study. First, all participants will be recruited from first-year university students in Beijing; thus, the sample might not be representative of the subclinical depression population in China. However, in light of the findings that the onset age of depression is during teenage years (37), adolescents and young adults are a high-risk population for subclinical depression. Moreover, university students from the three universities were recruited across the whole country; therefore, it is representative to a certain extent. Second, although the length of treatment and follow-up period (i.e., after the 8-week intervention, participants will be followed up for 1 year) is sufficient to demonstrate treatment effect, due to the relatively short follow-up period, the long-term effect of the intervention cannot be evaluated in this study.

To our knowledge, this is the first study to innovatively develop and test an intervention to improve psychological well-being and decrease the incidence of MDD in subclinical depression population. Once proven effective and acceptable, MoodBox could be potentially integrated into the routine clinical service to facilitate the management for people with subclinical depression.

## Ethics Statement

The study will be performed according to the ethical standards stated in the Declaration of Helsinki and its subsequent updates. All participants will be provided with an overview of the study's aims and characteristics summarized in the Informed Consent Form (ICF) and will be obtained written informed consent. The voluntary character of the study will be specified, indicating that withdrawal from the study is permitted at any time, without interfering with the usual treatment. The Ethics Committee Board of Beijing Anding Hospital approved the study protocol on 4 January 2020 (No. 202006FS-2).
